### Early termination

The criteria for premature discontinuation of further study medication for an individual participant in arm 1 are as follows: treatment-related toxicity, requirement for prohibited concomitant medications, clinical reasons believed to be life-threatening by the physician, even if not addressed in the toxicity section of the protocol.

The participant will continue to be followed with the participant’s permission if the study medication is prematurely discontinued. If the participant discontinues study medication between scheduled visits, the investigator may request that the participant visit the clinic as soon as possible for lab and safety assessments and to return the study medication for accountability purposes. There will be no changes to the follow-up visit schedule, except no study medication will be administered. If the participant chooses not to remain in the study, then the participant will be withdrawn from the study and participant will be asked to come in for an early termination visit.

The criteria for permanent withdrawal from the study for an individual participant are as follows:

loss to follow-up, pregnancy or suspected pregnancy, HCV treatment required for >12 weeks, request of the participant to withdraw from the trial, any clinical AE, laboratory abnormality, intercurrent illness, other medical condition or situation occurs such that continued participation in the study would not be in the best interest of the participant, the participant is judged by the investigator to be at significant risk of failing to comply with the provisions of the protocol as to cause harm to self or seriously interfere with the validity of the trial results, progression of diabetes requiring additional diabetes medication (i.e. oral diabetes medications or insulin therapy).

In the event that the participant is withdrawn from the study due to an AE, this must be recorded on the case report form (CRF). The subject should be followed and treated by the investigator until the abnormal parameter or symptom has resolved or stabilized.

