### Study design and setting

This study is a prospective 48-week single-centre, randomized, open-label, controlled trial of HIV-HCV co-infected and HCV mono-infected patients with IR (HOMA-IR ≥ 2.0) who are planning to initiate HCV antiviral therapy.

Sixty (60) participants meeting eligibility criteria will be randomized in a 1:1 ratio using variable block sizes to either arm 1, metformin 2 g [1 g twice a day (BID)] plus lifestyle, or to arm 2, lifestyle alone (the control arm). Randomization will be stratified according to HIV status and according to stage of liver fibrosis (F0–2 vs. F3–4) and will be conducted utilizing a web-based randomization system. The allocations will be generated by a statistician unassociated with the study using the SAS statistical program (SAS Institute, Inc., Cary, NC, USA) and uploaded into the randomization system. A log of all transactions including date and time of randomization, stratum and treatment allocation will be recorded. The randomization system will be accessed by the study coordinator at the study site when they have identified consenting eligible participants ready to be randomized.

Arm 1 (Metformin group) will receive metformin and lifestyle treatment during a 12-week period prior to starting HCV therapy (week 0–12), during the 12-week treatment phase (week 12–24) and 24 weeks post HCV treatment (week 24–48). Participants who require > 12 weeks of HCV treatment will be excluded. If initiation of HCV treatment is delayed beyond 12 weeks, participants will continue on metformin during this time period and will receive less metformin post HCV treatment. Arm 2 (Control group) will receive lifestyle treatment alone during a 12-week period prior to starting HCV therapy (week 0–12), during the 12-week treatment phase (week 12–24) and 24 weeks post HCV treatment (week 24–48). A detailed study flow chart is depicted in Fig. 1.

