### Sample size calculation

To date there have been no studies that have investigated the benefits of improved IR in the HIV-HCV co-infected population or in HCV mono-infected patients. Studies that have investigated the effects of HCV antiviral therapy on FibroScan® score reported a 32 % reduction in mean score (10.6 +/- 4.8 kPa) compared with baseline in patients that obtained a treatment response [37]. Based on these study results, a sample size of 24 participants in each group would provide approximately 80 % power to detect a 4 kPa difference between the two treatment arms assuming a similar standard deviation. We anticipate a 20 % loss to follow-up, so an additional six participants will be randomized per group to account for loss to follow-up and to allow secondary outcome analyses. Using regression of the final measurement on the initial measurement will likely improve the power relative to using simple difference scores.

All analyses will be based on intention-to-treat basis and per protocol analysis. Intention-to-treat population will be defined as the set of all patients randomized.

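### Permanent study withdrawal for diabetes progression and other post-randomisation events removes week-48 scans that the intention-to-treat analysis needs, and the loss may be informative

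*Protocol article*

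**What the plan says.** The Early termination section of the protocol article treats two events differently.

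- **Stopping study medication (arm 1).** "The participant will continue to be followed with the participant’s permission if the study medication is prematurely discontinued", and the visit schedule stays as it was.
- **Leaving the study.** A second list opens with "The criteria for permanent withdrawal from the study for an individual participant are as follows". It includes "HCV treatment required for >12 weeks", "progression of diabetes requiring additional diabetes medication (i.e. oral diabetes medications or insulin therapy"), and the case where "the participant is judged by the investigator to be at significant risk of failing to comply with the provisions of the protocol". The compliance item is qualified: the risk must be such as to harm the participant or seriously damage the trial's validity. Loss to follow-up, pregnancy, withdrawal of consent and a best-interest clause are also listed.

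After withdrawal, follow-up is described only for adverse-event cases, until the abnormality resolves or stabilises. An early termination visit is mentioned for participants who choose to leave. Neither is a week-48 scan.

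Other sections bear on this:

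- **Study design and setting:** "Participants who require > 12 weeks of HCV treatment will be excluded", without saying whether this means before or after randomisation. The trial is open-label, and HCV therapy is planned to start at week 12.
- **Sample size calculation:** "Intention-to-treat population will be defined as the set of all patients randomized". A 20 % loss to follow-up is allowed for.
- **Statistical analysis:** all analyses are by intention to treat. The primary model is a baseline-adjusted linear regression at week 48. Multiple imputation for missing week-48 scores is a sensitivity analysis, and a mixed model covers weeks 12 to 48. A per-protocol analysis is also planned.

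**The concern.** Because stopping the drug explicitly leaves follow-up intact, permanent withdrawal from the study must mean something more. Followed as written, it gives up the primary outcome of people who can be reached and may still consent. The plan itself would then create gaps in the set that it promises to analyse.

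The diabetes item matters most because it can depend on both arm and outcome. Arm 1 already takes metformin, so for that arm additional medication means a further drug. In arm 2 the first diabetes drug triggers removal. Metformin is expected to improve glucose handling, and the Background calls insulin resistance a major determinant of fibrosis. The controls removed could therefore be those with the worst fibrosis course. Entry allows HbA1c up to 8.0 %, and glucose is measured at every visit, so cases would be found.

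The compliance item rests on a judgement made with knowledge of the arm. The HCV-duration item can arise after randomisation, although nothing in the article ties it to arm.

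At stake is the comparability of the arms at week 48, in a trial planned on only 24 evaluable participants each.

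**Working it through.** **1. The plan's own figure.** Inputs from the Sample size calculation section: difference 4 kPa, SD 4.8 kPa, power about 80 %. A two-sided alpha of 0.05 is assumed.

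- Normal approximation: n = 2 × (1.960 + 0.842)² × 4.8² / 4² = 22.6, so 23 per group.
- t-test: 23.6, so 24 per group, with power 0.807.
- With 20 % loss: 24 / (1 − 0.20) = 30 per group, 60 in total.

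The stated sample size reproduces. The 20 % allowance protects precision and does nothing about selective loss.

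**2. Who enters the primary model.** Imputation is described as the sensitivity analysis that brings in participants without a week-48 score. It follows that the primary week-48 regression leaves them out. A participant withdrawn before week 48 is in the intention-to-treat set by definition but absent from the primary estimate.

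**3. Size if the worst controls leave.** Two inputs are assumptions that the documents do not give: the share p of controls withdrawn, and the correlation r between metabolic severity and week-48 kPa. If the top fraction p on a normal severity scale is removed, the retained control mean moves by

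shift = −r × SD × φ(z) / (1 − p), where z is the (1 − p) normal quantile and φ is the normal density.

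| p | φ(z)/(1 − p) | r = 0.3 (r × SD = 1.44) | r = 0.5 (r × SD = 2.40) |
|---|---|---|---|
| 10 % | 0.1755/0.90 = 0.195 | −0.28 kPa | −0.47 kPa |
| 15 % | 0.2332/0.85 = 0.274 | −0.39 kPa | −0.66 kPa |

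Against the 4 kPa target this is 7 % (0.28/4) to 16–17 % (0.66/4). Against the standard error of the difference, 4.8 × √(2/24) = 1.39 kPa, it is 0.20 to 0.47 standard errors.

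**4. Allowing losses in both arms.** With no true effect, the bias in those retained (metformin minus control) is (pC − pM) × D. Here pC and pM are the shares withdrawn from control and metformin, and D is how much worse the withdrawn participants' kPa change is than that of those retained. All three are assumed.

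| pC | pM | D = 2 | D = 4 | D = 8 |
|---|---|---|---|---|
| 10 % | 0 % | +0.20 | +0.40 | +0.80 |
| 10 % | 3 % | +0.14 | +0.28 | +0.56 |
| 20 % | 5 % | +0.30 | +0.60 | +1.20 |

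A positive value works against metformin, since lower kPa is better. If more participants with a poor course leave the metformin arm, pC − pM turns negative and so does the bias: 0 % against 10 % at D = 4 gives −0.40 kPa.

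**5. Power.** At the plan's final alpha of 0.048 (two-sided assumed), t-test power is 0.802 with 24 per arm. If mandated withdrawals came on top of the 20 %, a further 5 % or 10 % of 30 would leave 22.5 or 21 per arm, with power 0.774 or 0.744.

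**The case against.** The other side has several sound arguments.

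- **Intention to treat is not impossible.** A reader might infer that the analysis cannot be by intention to treat at all. The article does not support that. Withdrawn participants stay in the randomised set, the imputation analysis includes them, the mixed model uses their earlier scans, and the interim analysis also imputes. The conflict is with the primary week-48 regression.
- **Missing at random may be reasonable.** Loss driven by recorded glucose, insulin and HbA1c can be missing at random if the imputation model uses them. The article does not give that model, and it may properly sit in the analysis plan. What stands is that the repair depends on an assumption that cannot be checked once outcome collection stops.
- **Diabetes withdrawals may be few.** Pre-existing diabetes and any current or past diabetes drug are exclusions. The 10–15 % shares, 3 to 4.5 of 30 controls, have no source in the article.
- **HCV duration is a weak example.** Entry already requires an intended course of 8–12 weeks, and the exclusion in Study design and setting can be read as eligibility.
- **The compliance rule is narrower than mere expected non-adherence,** because of its harm-or-validity qualifier.
- **A definite power loss might be inferred.** That needs the 20 % allowance to exclude mandated withdrawals, which the article does not say. Baseline adjustment would also recover some power.
- **The two Early termination rules do not contradict each other.** They apply to different events.

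These arguments limit the point. They do not explain why a reachable, consenting participant who starts a diabetes drug should lose the week-48 scan.

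**Conclusion.** The concern holds, as something that should be fixed. The withdrawal list, chiefly its diabetes item, conflicts with the promise to analyse everyone randomised, because the primary week-48 regression omits those withdrawn. The loss is plausibly related to both arm and outcome.

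Under the assumed truncation the control mean shifts by about 0.3–0.7 kPa against a 4 kPa target. That is modest beside a standard error of 1.39 kPa, but avoidable. It rests on an assumed withdrawal share and correlation, on no matching loss in the metformin arm, and on an SD not reduced by baseline adjustment.

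A reader might infer that the rule favours metformin or threatens a false positive. The documents do not support that. Diabetes withdrawals alone would work against metformin, adverse-event or compliance withdrawals could act the other way, and the net direction is unknown.

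**What to change.** Reconcile Study design and setting, Sample size calculation, Statistical analysis and Early termination by separating treatment decisions from outcome collection:

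- Participants who meet the diabetes-progression, HCV-treatment-length or compliance criterion, and who still consent and can safely attend, keep the scheduled FibroScan and laboratory assessments to week 48.
- They are analysed in their randomised arm, with the event and its date recorded.
- The exclusion for HCV treatment longer than 12 weeks is stated to apply before randomisation.

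The clinical rules, including those on pregnancy and on the participant's best interest, remain for the sponsor.

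The cost is small. The article states that recruitment has yet to begin, the change is one of wording, and the scans are already in the schedule of events. The downside is one of interpretation. The estimate becomes a treatment-policy effect that includes participants who start other diabetes drugs, which may dilute the contrast. The per-protocol analysis already planned covers the alternative question.

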### Trial registration and dissemination

This study has been registered with ClinicalTrials.gov (Identifier Number NCT02306070, https://clinicaltrials.gov/ct2/show/NCT02306070). A SPIRIT checklist is provided as an additional file (see Additional file 1). The findings of this trial will be submitted to a peer-reviewed journal and abstracts will be presented at relevant national and international conferences.

## Discussion

HCV antiviral therapy has evolved rapidly in recent years and access to these medications has improved. While SVR is associated with improved liver outcomes, the rate of liver fibrosis regression with SVR is variable and predictors of regression are not well established [32]. In addition, achieving SVR in patients with cirrhosis does not necessarily prevent decompensation or eliminate the risk of HCC. A better understanding of the role insulin resistance and impaired glucose metabolism have on these outcomes in HCV patients who achieve SVR are needed.

Identifying and targeting potentially modifiable risk factors such as IR and T2DM may be of significant importance in preventing progression of and promoting regression of liver fibrosis, reducing mortality and improving outcomes for HCV-HIV co-infected and HCV mono-infected patients.

This pilot study will be the first to evaluate the role of metformin on liver fibrosis in HCV-HIV co-infected and HCV mono-infected patients with IR receiving DAA HCV treatment. If metformin is effective in reducing liver fibrosis in this patient population, this will represent a well-tolerated, easy-to-administer, inexpensive therapy that will protect against negative HCV outcomes. This study will also be an opportunity to evaluate the impact of insulin resistance and hyperglycemia on viral clearance in HCV-infected patients treated with interferon-free regimens. In addition, the study will further explore the relationship between HCV, insulin resistance and AFP levels. This knowledge will inform patient care, translate into improved therapeutic outcomes for liver and metabolic diseases, and guide further innovative research in this area.

## Trial status

Recruitment for this study will begin in July 2016.

## Abbreviations

AE, adverse event; AFP, alpha-fetoprotein; AMPK, AMP-activated protein kinase; APRI, AST to platelet ratio index; ART, antiretroviral therapy; BID, twice daily; BMI, body mass index; CBC, complete blood count; CrCl, creatinine clearance; CRF, case report form; CRP, C-reactive protein; CTN, Canadian HIV Trials Network; DAA, direct-acting antivirals; DSMC, Data and Safety Monitoring Committee; eGFR, estimated glomerular filtration rate; HBV, hepatitis B; HCC, hepatocellular carcinoma; HCV, hepatitis C; HDL-c, high density lipoprotein cholesterol; HIV, human immunodeficiency virus; HOMA-IR, homeostatic model assessment of insulin resistance; HSC, hepatic stellate cells; ICH, International Conference on Harmonization; IDU, illicit drug use; IFN, interferon; IL-6, interleukin 6; IL-8, interleukin 8; INR, international normalized ratio; IR, insulin resistance; IRB/REB, institutional review board; kPa, kilopascal; LDL-c, low-density lipoprotein cholesterol; mTOR, mammalian target of rapamycin; N, number; OGTT, oral glucose tolerance test; PI, principal investigator; QD, once daily; REB, research ethics board; SAE, serious adverse event; SOP, standard operating procedure; SVR, sustained virological response; T2DM, type 2 diabetes; TGF-β, transforming growth factor beta; TID, three times daily; TNF-α, tumour necrosis factor alpha; WHO, World Health Organization
